### Genotyping and bioinformatic analysis

Peripheral whole blood will be collected and labeled with a unique barcode to ensure anonymization and unbiased assessment. High quality genomic DNA will be extracted using commercial kits (Qiagen) and will be quantified by spectrophotometry using Nanodrop 1000 (Thermo Fisher). Ultrasensitive targeted NGS of extracted DNA (40 ng) will be performed using custom QIAseq Targeted DNA Panel (Qiagen) containing primers for the enrichment of the 228 SNPs of interest. The produced molecularly barcoded libraries will be quantified by Qubit 3 Fluorometer (Invitrogen) and real time PCR (QIAseq Library Quant Assay kit). Sequencing will be performed by sequencing by synthesis (SBS) chemistry on MiniSeq Platform of Illumina using the MiniSeq Mid Output Kit (300-cycles). The generated NGS data (in fastq format) will be analyzed with the CLC Genomics Workbench (Qiagen) bioinformatics software and the genotype of each SNP will be determined.

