### Statistical considerations

#### Sample size estimation and endpoints of the study

The primary endpoint of the study is to discover potential correlations of the SYNTAX score with patients' genomic profile and create a blood-based gene expression test (genetic SYNTAX score) which could accurately identify patients at high risk for CAD of moderate or high severity. For the estimation of the sample size the G*Power [25, 26] and Epi Info (StatCalc) [27] software tools were used. To this regard, we made use of the exact sampling distribution of the squared multiple correlation coefficient implemented in G*Power assuming 250 predictors, a two-tailed test, power of 0.9, significance level of 0.05, ρ^2^ = 0.13 and a ratio of unexposed to exposed equal to 2 (based on a pilot study on 100 patients). The initial sample size was finally increased by 10% because of the possibility that some patients might be lost to follow-up. Hence, we aim for a total sample of 1080 patients.

Secondary endpoints of the study are the development of a panel of genetic markers that, in conjunction with clinical parameters, could strongly predict the occurrence of MACCE or any bleeding events during follow up.

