The model building process will be based on *Hurdle Models* that are a class of modeling techniques able to handle excess zeros and overdispersion of SYNTAX score variable. Describing briefly, the *Hurdle Model* has two parts: (*i*) a *zero hurdle part* which models the right-censored outcome SYNTAX score variable indicating patients with a zero-count ($$Y = 0$$) or patients with a positive count ($$Y = 1$$), where all values larger than zero are censored (i.e. fixed at one) and (*ii*) a *truncated count part* modeling the total number of SYNTAX score for patients presenting a non-zero count ($$Y > 0$$). Regarding the identification of the best set of predictors for each part of the model, a feature selection search strategy based on *Akaike Information Criterion* will be utilized, in which the set of predictors are included in the *full model* and at each step of the iterative process, a predictor is dropped out. To assess the fitting performance of the final model, well-known evaluation metrics for regression (e.g. mean and median squared, absolute and percentage errors) and classification tasks (*accuracy*, *F*-*measure*, *G*-*mean*, *precision* and *recall*) will be used, whereas for the evaluation of the prediction performance of the model, data-generating schemas (i.e. *holdout* and *k-fold cross-validation*) that split the available dataset into training and test sets will be performed. In addition, graphical evaluation of model’s performance will be assessed through appropriate visualization methods, such as *Receiver Operating Characteristic* (ROC) and *Precision-Recall* curves for the zero-hurdle part and *Regression Error Characteristic* (REC) curves for the truncated count part.

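### Backward AIC elimination without shrinkage, started from about 250 predictors in each hurdle part, is expected to give an overfitted and badly calibrated genetic SYNTAX score

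*Protocol article*

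**What the plan says.** The Statistical analysis section of the protocol article specifies a two-part hurdle model for the SYNTAX score: a zero part, and a truncated count part "modeling the total number of SYNTAX score for patients presenting a non-zero count". Predictors are chosen separately for each part by AIC. All predictors enter the full model, and "at each step of the iterative process, a predictor is dropped out". The coefficients that remain are not said to be shrunk or penalised. The univariable tests described just before are not presented as a filter on the candidate set.

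The scale comes from two other places. The sample-size paragraph proceeds by "assuming 250 predictors, a two-tailed test, power of 0.9, significance level of 0.05", with "ρ^2^ = 0.13 and a ratio of unexposed to exposed equal to 2", and arrives at 1080 patients. The genotyping section describes a panel "containing primers for the enrichment of the 228 SNPs of interest".

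The plan evaluates the model with squared, absolute and percentage errors, classification measures, ROC and precision-recall curves, and validates it by holdout and k-fold cross-validation. It does not say that selection is repeated inside the folds.

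**The concern.** For a single coefficient AIC is a lenient criterion. Applied backwards to some 250 candidates, twice, it lets many chance associations through. The survivors keep full-size coefficients that were selected partly because they were overestimated. The count part repeats the exercise on the non-zero patients only.

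The genetic SYNTAX score is the primary product of the study. If its coefficients are too large, predicted severity is spread too widely: patients are placed too far above or below the average, and squared error in new patients can exceed that of giving everyone the mean.

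**Working it through.** **Inputs from the document:** 250 predictors, of which 228 are SNPs; ρ² = 0.13; N = 1080; backward AIC from the full model in each part. The SYNTAX score comes from the angiogram at enrolment, so no loss to follow-up is deducted.

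**Assumptions, because the document gives no figure:** number of truly active predictors (5, 20, 100 or all 250); independent SNPs with minor-allele frequency 0.05 to 0.5; for the hurdle runs, 60% to 75% non-zero scores (648 to 810 of 1080 patients) and negative binomial dispersion 2.

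**The plan's own figure.** The exact test of the squared multiple correlation with these inputs needs 657 patients (upper-tail 0.05) or 716 (two-tailed). With the 10% allowance this is 657 × 1.1 = 723 to 716 / 0.9 = 796, so 1080 is not reproduced. That is a separate matter. The check below uses 1080, which favours the plan.

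**Step 1: the implied threshold.** AIC drops a 1-df term when twice the loss in log-likelihood is below 2. For a null term P(χ²₁ > 2) = 0.157. Expected null terms kept: 0.157 × 228 = 36, or 0.157 × 250 = 39. A simulated backward search with no signal kept 51. The excess arises because a full model of 250 terms understates the residual variance: in the linear case the cut-off for t² at the start is about 2 × (1080 − 251)/1080 = 1.54, not 2.

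**Step 2: linear analogue, n = 1080, true R² = 0.13 (100 runs per setting).** With 5 to 100 active predictors, 55 to 73 terms are kept, 32 to 50 of them noise. If all 250 are active, about 77 are kept. A second linear simulation gave 53 to 78 terms, apparent R² 0.26 to 0.28, new-patient R² -0.02 to -0.11 and slope 0.34 to 0.47. Backward AIC against ridge on the same data:

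| Active predictors | AIC: new-patient R² | AIC: calibration slope | AIC: correlation with outcome | Ridge: new-patient R² |
|---|---|---|---|---|
| 5 | -0.026 | 0.46 | 0.239 | +0.044 |
| 20 | -0.033 | 0.45 | 0.240 | +0.048 |
| 100 | -0.075 | 0.38 | 0.212 | +0.048 |
| 250 | -0.098 | 0.34 | 0.183 | +0.045 |

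Across the simulations, new-patient R² was below zero in 75% to 100% of runs.

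**Step 3: two-part hurdle, N = 1080, true overall R² about 0.14 (8 runs per setting, 5 to 100 active predictors).**
- Zero part: 49 to 65 terms kept, Brier skill -0.11 to -0.18.
- Count part: 42 to 56 terms kept, R² -0.11 to -0.45.
- Combined score: R² -0.04 to -0.17, below zero in 62% to 100% of runs.

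A second implementation at a higher true R² (0.16 to 0.18; 12 runs per setting) gave a combined R² of -0.03 to -0.15, with nearly all of the damage in the count part (zero-part Brier skill 0.00 to -0.09). The direction of the combined result is stable. How the damage divides between the parts is not.

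**Step 4: ranking, linear analogue, AUC for the top quartile (25 runs; lasso only 4).**

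| Active predictors | Backward AIC | Ridge | Lasso |
|---|---|---|---|
| 20 | 0.611 | 0.604 | 0.626 |
| All 250 | 0.592 | 0.606 | 0.573 |
| 3 strong + 20 weak | 0.616 | 0.607 | 0.656 |

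**Step 5: what simple recalibration recovers.** Multiplying the AIC predictor by the correct single shrinkage factor gives R² of about the squared correlation: 0.240² = 0.058 with 20 active predictors (ridge 0.048), and 0.183² = 0.033 with all 250 active (ridge 0.045).

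**The case against.** The strongest reply is that the primary endpoint is about identifying patients with moderate or high severity, which is discrimination, while a negative R² is largely a matter of calibration slope. This stands in part. Step 4 shows that AIC selection ranks patients about as well as ridge, and better than lasso when effects are diffuse. In the hurdle runs of step 3 with true R² about 0.14, the AUC for a SYNTAX score above 22 was 0.61 to 0.65. A reader might infer that the score is useless in new patients; the figures do not support that. But squared error is among the plan's own metrics, and a slope below one half misstates individual severity whatever the ranking.

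Second, the plan separates fit from prediction and schedules holdout and cross-validation, so the apparent R² need not be what it reports as predictive performance. That is fair. Validation would reveal the problem if selection is repeated in each fold, which the text does not say. It would not correct the coefficients.

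Third, the modelling paragraph gives no candidate count, and a fuller analysis plan may narrow the set. The 250 is an inference and has to be labelled so.

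Fourth, step 5 shows that a single shrinkage factor repairs much of the damage. Replacing the whole method is therefore not the only remedy.

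**Conclusion.** The point holds as one of overfitting and miscalibration. At the plan's own ρ² and 1080 patients, the stated rule roughly doubles the apparent R² (0.26 to 0.28 against a true 0.13), gives a mean new-patient R² of about -0.02 to -0.11 in the linear analogue, and needs its coefficients cut by more than half (slope 0.34 to 0.47). The count part has fewer patients and does worse, by an amount that depends on the unstated share of zeros.

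This rests on about 250 candidates entering each part, on independent SNPs and on small hurdle simulations. Three stronger readings should be avoided:
- Prediction worse than the mean is an average result, not a certainty. With five strong predictors about 20% of linear runs, and 3 of 8 hurdle runs, stayed at or above zero.
- Dozens of noise SNPs follow only if most candidates are null for the SYNTAX score. If all 250 carry signal, none of the retained terms is noise, yet new-patient R² is still negative.
- Much lower values of R² (-0.28 to -0.34) arise in a linear analogue with 589 patients. That describes one part only, assumes 40% zeros, and starts from 982 patients by deducting follow-up loss that does not affect an enrolment outcome.

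This is a worthwhile and cheap improvement to the primary deliverable, not a defect that invalidates the study.

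**What to change.** In the model-building paragraph of the Statistical analysis section, replace the AIC search by penalised estimation of each hurdle part:

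- Use elastic net, with both the ridge-lasso mix and the penalty tuned by cross-validation inside the training data. Lasso alone is weak if effects are diffuse.
- Repeat all selection and tuning inside every fold or holdout split.
- Report the penalised coefficients as the score, together with the calibration slope in held-out data.
- Keep backward AIC as a sensitivity analysis.
- State how many candidate predictors enter each part.

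If the AIC search is retained as the main method, the minimum is a shrinkage factor estimated by cross-validation, with the search repeated in each fold, and applied to the final model.

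No extra patients or data are needed. The costs are that penalised coefficients come without conventional p-values, and that the truncated count part needs a less common R routine than the zero part, which is ordinary penalised logistic regression.

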## Abstract

**Background:**

Coronary artery disease (CAD) remains one of the leading causes of mortality worldwide and is associated with multiple inherited and environmental risk factors. This study is designed to identify, design, and develop a panel of genetic markers that combined with clinical and angiographic information, will facilitate the creation of a personalized risk prediction algorithm (GEnetic Syntax Score—GESS). GESS score could be a reliable tool for predicting cardiovascular risk for future adverse events and for guiding therapeutic strategies.

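### The measures named for the zero-hurdle probabilities judge only labels and ranking, so they cannot show that predicted risks are too extreme, which backward AIC from about 250 predictors makes likely

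*Protocol article*

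**What the plan says.** The Abstract (Background) presents the product as a tool that will "facilitate the creation of a personalized risk prediction algorithm" and adds that the "GESS score could be a reliable tool for predicting cardiovascular risk for future adverse events and for guiding therapeutic strategies".

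The Statistical analysis section fixes how the SYNTAX model is built and judged:

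- **Selection.** AIC is used with backward elimination: "the set of predictors are included in the *full model* and at each step of the iterative process, a predictor is dropped out". The sample size section assumes 250 predictors. No shrinkage is mentioned.
- **Numerical measures.** "well-known evaluation metrics for regression (e.g. mean and median squared, absolute and percentage errors) and classification tasks". The regression errors are given as examples. The five classification measures (accuracy, F-measure, G-mean, precision, recall) are listed without such wording.
- **Graphs.** ROC and precision-recall curves for the zero part and REC curves for the count part, all introduced as examples.
- **Validation.** Data-splitting schemes, "i.e. *holdout* and *k-fold cross-validation*) that split the available dataset into training and test sets will be performed".

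For follow-up, the same section plans Kaplan–Meier curves, log-rank tests and a Cox model, and names no performance measure for the Cox model. The article names no calibration plot, slope, intercept or Brier score, and states no performance level at which the score would be accepted.

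**The concern.** A personalised risk score is used through the probability it gives to one patient. The five classification measures see only which side of a cut-off that probability falls on, and the ROC and precision-recall curves see only its rank. A model can therefore give probabilities far too close to 0 or 1 while every measure named for the zero part stays the same.

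The selection procedure makes this distortion likely. Eliminating by AIC from about 250 candidates keeps terms partly because their estimates are large by chance, and nothing then shrinks them. Accuracy and F-measure also have a floor set by prevalence, so a moderate value can look respectable for a score that is worse than calling everyone positive.

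At stake is a score reported with individual risks that overstate how far patients differ.

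**Working it through.** The plan gives no performance figure to reproduce. Its sample size serves only to set the scale, and whether 1080 follows from the stated inputs is a separate question.

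**Inputs from the article.** 1080 patients after a 10% increase, so 1080/1.1 ≈ 982 before it; 250 predictors, of which 228 are SNPs, leaving 22; ρ² = 0.13; backward AIC.

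**Assumed inputs.** The share of patients with SYNTAX above zero (33%, 63% and 67% tried); ρ² = 0.13 carried over as the latent R² of the zero part; the remaining 22 predictors being clinical; in one simulation, a split of R² into 0.05 and 0.08 between SNPs and clinical predictors. The 2:1 ratio in the sample size section is unexposed to exposed, so it does not give the prevalence.

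**Step 1: can the zero-part measures see over-extreme risks?** Take a well-calibrated logit, multiply it by k and classify at 0.5. The sign of the logit and the order of patients do not change, so neither do labels and ranks. Simulated with 200,000 patients:

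| k | Accuracy | F | G-mean | Precision | Recall | AUC | Brier (not in plan) |
|---|---|---|---|---|---|---|---|
| 1 | 0.697 | 0.788 | 0.576 | 0.719 | 0.871 | 0.722 | 0.197 |
| 2 | same | same | same | same | same | same | 0.210 |
| 3 | same | same | same | same | same | same | 0.227 |
| 5 | same | same | same | same | same | same | 0.249 |

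ROC and precision-recall curves are unchanged by any strictly increasing distortion. The exact invariance of the five label measures assumes the 0.5 cut-off and stretching about logit 0. At another fixed cut-off they may move, but they still do not measure calibration.

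**Step 2: the count part.** With an illustrative mean of about 12 (assumed), over-spreading the linear predictor by 1, 2 and 3 moves RMSE from 12.28 to 16.75 to 44.34 and mean absolute error from 8.50 to 10.85 to 18.89. The named error measures do react here, although they do not separate miscalibration from noise.

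**Step 3: how likely is the distortion at this scale?** Logistic zero part, 982 patients, backward AIC, fresh test data. The calibration slope comes from regressing the new outcomes on the predicted logit. The prevalence-only Brier score is p(1 − p).

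- *About 63% positive, 250 SNP-type predictors, 12 runs:* mean slope 0.17 after elimination (range 0.09 to 0.21) and 0.14 for the full model. AUC is 0.573, against 0.681 for the true predictor. Brier is 0.274, against 0.632 × 0.368 = 0.233.
- *67% positive, 228 + 22 predictors, 8 cohorts:* slope 0.19, AUC 0.58, Brier 0.253 against 0.667 × 0.333 = 0.222. Top risk decile: predicted 97%, observed 77%. Bottom decile: predicted 18%, observed 56%.
- *33% positive, same design:* slope 0.18, Brier 0.256 against 0.222. Top decile: predicted 83%, observed 44%.
- *A further simulation at the same size:* slope about 0.13 to 0.17, Brier 0.255 to 0.261 against 0.221. Rescaling by the cross-validated slope brought Brier to about 0.219.

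To read a slope of 0.17: two patients whose predicted odds differ tenfold have true odds that differ by about 10^0.17 ≈ 1.5.

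**Step 4: what the named measures would show.** Calling everyone positive at p = 0.667 gives F = 2p/(1 + p) = 1.333/1.667 = 0.80 and accuracy 0.67. The simulated model has F 0.733 and accuracy 0.62. From F = 2TP/(2TP + 1 − accuracy), 2TP = 0.733 × 0.38/0.267 = 1.043, so TP = 0.522 and recall = 0.522/0.667 = 0.78. True negatives are 0.62 − 0.522 = 0.098, so specificity = 0.098/0.333 ≈ 0.29 and G-mean = √(0.78 × 0.29) ≈ 0.48, about that of a coin toss (0.50).

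**The case against.** The strongest reply is that the plan's own measures would expose the simulated score. Under the planned cross-validation its AUC is near 0.58, its G-mean is near 0.48, and its accuracy is below the base rate. G-mean and AUC have no prevalence floor. This stands: a reader might infer that a useless score would pass unnoticed, and the working does not support that. What these measures cannot show is that the probabilities are too extreme, and Step 1 shows that this holds for a model that discriminates better as well.

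Three further limits stand:

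- A reader might infer that a miscalibrated score would be accepted. The article states no acceptance rule, so nothing supports this.
- A reader might infer that no measure in the plan reacts. The squared and absolute errors do, in the count part.
- Part of the primary aim is to identify patients with moderate or high severity, a task that classification measures suit. The zero part predicts only SYNTAX above zero; risks of future events would come from the Cox model.

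It can also be said that calibration statistics belong in an analysis plan that is not shown, and that the regression and graphical lists are open. So only their absence from this article is established. The article does, however, commit to a selection method that tends to give over-extreme risks and to a detailed set of measures, and none of those named for the zero part can see that fault. That is a choice already made, not silence. The Cox gap alone would not be a finding.

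**Conclusion.** The point holds for the predicted probabilities of the zero-hurdle part. The named classification measures and curves cannot reveal over-extreme risks, and the stated selection procedure makes such risks likely. Under the assumed inputs the calibration slope in new data is about 0.1 to 0.2, and the Brier score exceeds the prevalence-only value by about 0.03 to 0.04 (0.253 against 0.222; 0.274 against 0.233). The direction was the same at 33%, 63% and 67% positive. The size depends on the assumed R² and on few simulated cohorts, so it is indicative.

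This does not show that the plan would accept or conceal a weak score, or that the count part is unprotected. It is worth correcting before analysis, because it changes the individual risks that are reported.

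**What to change.** In the hurdle-model paragraph of the Statistical analysis section:

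1. Add the calibration intercept, slope and smoothed curve for the zero-part probabilities, and the Brier score beside the prevalence-only value p(1 − p). Compute them on the cross-validated predictions already planned, with the AIC selection repeated inside each fold.
2. Rescale the final score by the cross-validated slope and intercept before reporting it.
3. Show accuracy and F-measure beside the values obtained by calling every patient the same.

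In the survival paragraph, apply the same calibration checks to any individual 1-year MACCE or bleeding risk reported from the Cox model. This needs cross-validation to be added there, as none is named for that model.

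For the zero part the cost is a few lines of text and R code, with no new data. The Cox model needs somewhat more work. The downside is that reported performance will look less favourable. Rescaling corrects the size of the risks but does not improve discrimination: in the simulation it brought the Brier score only to about 0.219, against 0.221 for prevalence alone.

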*Survival analysis* methods will be also performed for examining patients at follow-up period. More specifically, the non-parametric *Kaplan–Meier* analysis will be conducted for graphically evaluating the survival function of patients, while *log-rank tests* will be conducted for investigating effects of different factors on survival distribution. Finally, *Cox Regression* analysis will be performed to build a multivariate regression model between several predictors and the survival time of patients.. Statistical analysis will be performed via the R statistical programming language. In all tests a difference will be considered as statistically significant when p-value (significance) will be less than 0.05, while all conducted tests will be two-tailed (non-directional).

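### As the plan is ordered, AIC selection precedes data splitting. Unless it is repeated inside each training set, the validated accuracy of the genetic SYNTAX score will be optimistic

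*Protocol article*

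**What the plan says.** The Statistical analysis section of the protocol article sets out the modelling of the SYNTAX score in this order:

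1. A hurdle model is built, with a zero part (score zero or positive) and a truncated count part for positive scores. For each part the best predictors are sought by AIC, starting from a *full model* and dropping one predictor at a time.
2. Regression and classification metrics are then named, introduced by "To assess the fitting performance of the final model".
3. For prediction performance, holdout and k-fold cross-validation schemes "that split the available dataset into training and test sets will be performed".
4. ROC and precision-recall curves (zero part) and REC curves (count part) are added, without saying whether they use training or test data.

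On the number of candidates, the genotyping section describes a panel "containing primers for the enrichment of the 228 SNPs of interest", and the sample size calculation was "implemented in G*Power assuming 250 predictors, a two-tailed test, power of 0.9, significance level of 0.05". The target is 1080 patients. The primary endpoint includes a blood test that accurately identifies patients at high risk of moderate or severe disease. No external validation cohort is described.

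**The concern.** Cross-validation gives an honest estimate only if every step that looked at the outcome is repeated without the test patients. Backward AIC elimination is such a step. If it is run once on everyone and only the coefficients are re-estimated within folds, the kept SNPs are those that happen to correlate with the outcome in the test patients as well. The test folds then confirm chance associations that they helped to create. A holdout split made after selection has the same defect.

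The section presents selection as model building and splitting as a later evaluation of the resulting model. An analyst who follows it in sequence would leak test information into the selection. Accuracy of the score is the study's main claim, and internal validation is the only safeguard the article describes, so the figure at risk is the one readers will rely on most.

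**Working it through.** The plan gives no figure for validated performance, so there is none to reproduce. The check asks how large the optimism would be at the planned size if selection came first.

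**Inputs from the article:** N = 1080, or 1080/1.1 ≈ 982 with the 10% allowance for loss to follow-up taken off; 228 SNPs, or 250 predictors as in the sample size statement; backward elimination by AIC; holdout and k-fold validation. Whether 1080 follows from the sample size inputs is a separate matter and is not used here.

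**Assumed, because not given:** share of zero scores 20%, 33%, 40% or 50%; 10 folds; a 70/30 holdout; independent SNPs with minor allele frequency 0.05 to 0.50; no clinical covariates; no SNP with any effect (true AUC 0.50).

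**Step 1: what AIC keeps by chance.** AIC retains a one-parameter predictor when its chi-square exceeds 2. For a null predictor, P(χ²₁ > 2) ≈ 0.157. A rough expectation is therefore 228 × 0.157 ≈ 36 null SNPs, or 250 × 0.157 ≈ 39. The simulations keep somewhat more, about 43 to 51, since the search starts from an overfitted model.

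**Step 2: zero part.** Logistic model; the predictor with the smallest Wald chi-square is dropped until all exceed 2. AUC = [R₁ − n₁(n₁+1)/2]/(n₁n₀), where R₁ is the rank sum of patients with a positive score. Coefficients were re-estimated in each training set throughout. Means over replicates:

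| N | SNPs | Zero share | Replicates | Null SNPs kept | CV AUC, selected on all data | CV AUC, selected in each fold | Holdout AUC, selected on all data |
|---|---|---|---|---|---|---|---|
| 1080 | 228 | 33% | 12 | 46 | 0.657 | 0.498 | 0.652 |
| 1080 | 250 | 33% | 8 | 51 | 0.668 | 0.490 | 0.640 |
| 1080 | 228 | 20% | 8 | 51 | 0.697 | 0.516 | 0.704 |
| 1080 | 228 | 50% | 8 | 43 | 0.644 | 0.489 | 0.634 |
| 982 | 228 | 40% | 48* | 46 | 0.656 | 0.500* | not run |

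*The in-fold figure for N = 982 used 5 folds and 12 replicates. In that setting the AUC on the data used for fitting was 0.73, and in new patients 0.50.

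A further run of three replicates (N = 1080, 228 SNPs, 33% zeros) gave about 53 SNPs kept and AUCs of about 0.67 and 0.51.

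**Step 3: is the gap simulation noise?** In the four N = 1080 scenarios, the largest between-replicate standard deviation of a cross-validated AUC is 0.022. With at least 8 replicates, the standard error of a mean is at most 0.022/√8 ≈ 0.008. The smallest gap is 0.644 − 0.489 = 0.155. Noise does not explain it.

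**Step 4: positive part.** With a Gaussian stand-in for the truncated count model, cross-validated R² = 1 − (test squared error)/(test squared error about the training mean). It was +0.07 to +0.13 with selection on all data and −0.25 to −0.54 with selection in each fold. The first looks like modest explained variation. The second shows that the selected model predicts worse than the mean, which is right when no SNP matters.

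**The case against.** The strongest reply is that the leak is inferred from sentence order. A condensed methods paragraph naturally describes the method and then its evaluation, without fixing the order of execution. A reader might infer that the plan selects predictors on the full dataset, but no sentence says so: *full model* means all predictors before elimination, not all patients. Repeating the elimination inside each training set is compatible with the wording. Fold number, split share and nesting are also details that an article may leave to a fuller plan. This stands as far as it goes, and it is why the point is conditional. It does not remove the point, because the article itself names the criterion, direction, metrics, resampling schemes and plots, and arranges them so that following them in sequence spoils the validation.

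A reader might also infer that the score is bound to look predictive, or that a worthless panel will be reported as useful. That goes too far. The figures assume that no SNP has any effect, whereas the panel was chosen from the literature as relevant to coronary disease. The simulations show the mechanism and its scale, not a forecast for this study.

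Finally, a reader might extend the criticism to the survival analysis, where Cox regression will "build a multivariate regression model between several predictors and the survival time of patients". That sentence describes no selection procedure, so no leak can be attributed to it, and its silence on validation is what an article may leave to the full plan. It forms no part of this point.

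**Conclusion.** The point holds in conditional form. The section introduces data splitting after the final model has been selected and nowhere confines selection to the training sets. If carried out in that order, validated performance will be optimistic. With no true SNP effect, the cross-validated AUC of the zero part would be about 0.64 to 0.70 (holdout about 0.63 to 0.70) instead of 0.50, and selection inside each fold restores it to about 0.49 to 0.52. The size rests on a global null, independent SNPs, no clinical covariates, assumed zero shares of 20% to 50%, a Wald approximation to AIC, and few replicates in most scenarios, so the values are approximate. The direction was the same in every setting tried. The wording should be settled before the score's accuracy is estimated.

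**What to change.** State in the Statistical analysis section that:

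- the entire AIC elimination, for both hurdle parts, is repeated inside every training fold;
- the holdout set is kept out of selection altogether;
- the nested estimate (or a bootstrap optimism-corrected one, with selection repeated in each bootstrap sample) is the primary performance figure, and the ROC, precision-recall and REC curves are based on it;
- metrics computed on the data used to select and fit the model are labelled apparent.

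If the full plan already does this, it is enough to say so. The cost is a few sentences and more computing time, since elimination runs once per fold instead of once. The reported accuracy will also be lower. No change to recruitment, genotyping or follow-up is needed.
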